### Data collection

Quality indicators collected for use in the feedback reports and related clinical measures are derived from routinely collected administrative data, linked using unique encoded identifiers at the Institute for Clinical Evaluative Sciences (ICES).

Data will be compiled from the following databases: (1) the Ontario Drug Benefits (ODB) database, covering nearly all prescriptions in nursing homes; (2) the Canadian Institute for Health Information (CIHI) databases covering all inpatient hospitalizations and emergency department visits; (3) the Ontario Health Insurance Plan (OHIP) database, covering physician billings; (4) the Registered Persons Database (RPDB) covering demographic information including date of death; and (5) the Continuing Care Reporting System (CCRS) database for clinical and demographic information on nursing home residents collected using the Resident Assessment Instrument (RAI). The RAI is legislatively required for each nursing home resident in the province within 2 weeks of admission date and then every 92 days, or any other time when the clinical condition of a resident considerably changes. The RAI captures a range of data such as functional and cognitive performance scales and can be used to determine date of admission and discharge from each nursing home [28].

HQO will track the unique College of Physician and Surgeons of Ontario (CPSO) numbers for those physicians who signed up for the reports. This will be encrypted and linked to the ICES Physician Database to assess physician characteristics, including age, sex, and whether they graduated from Canada or an international school. For each physician who signs up for the Practice Reports, HQO will also keep a file to track the number of times they downloaded the report at each quarterly release. This data will be confidentially shared with ICES analysts (keeping investigators blind), and the coded data will be used to conduct a sensitivity analysis to examine how intensity of exposure relates to effect size.

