We will examine whether the language in the key message in the report (i.e. the bolded statement declaring the number of additional/fewer patients are at risk from (or safe from risks of) benzodiazepines) is differentially associated with changes in prescribing. This is an uncontrolled element of the intervention, dependent on the observed distribution of performance of physicians relative to their peers. The relative performance of the physician compared to the comparator may act as an effect modifier because having additional patients at risk of harm or fewer patients safe from harm may invoke different responses than having fewer patients at risk or more patients safe. Additionally, it is plausible that recipients may respond more actively to simpler language (e.g. ‘7 additional residents in my practice may be at increased risk of harm’ may be easier to interpret than ‘7 fewer residents in my practice are safe from risk of harm’) because the simpler wording may make it easier for recipients to evaluate their performance relative to the comparator and respond accordingly. Thus, we will adjust for relative performance (i.e. better, same, or worse than comparator) and clarity of the statement (i.e. additional versus fewer) as a covariate and then conduct planned subgroup analyses to examine differential effects of the intervention across these subgroups (while acknowledging unmeasured confounding and uncertain power in these subgroup analyses).

We will also explore potential effect modification by baseline prescription rate, ownership status of nursing home, beds in the home, location (urban/rural), specialist utilization (proportion of patients with geriatrician or psychiatrist consultation within 6 months), plus primary physician characteristics (sex, years’ experience), as well as patient characteristics (age, sex, time at facility, levels of function and cognition). A planned sensitivity analysis will examine effects by extent of exposure to the intervention (i.e. fidelity of receipt, which assesses whether physicians downloaded their report).

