### Power

In head-to-head trials where small changes to existing initiatives are tested and where each sequential change in the process of optimization is expected to offer cumulative benefit, it is necessary to power for small changes. In this pragmatic trial, the sample size is dependent on the number of providers who sign up for the reports. At the time of study launch, there will be physicians working in over 200 nursing homes who have signed up to receive the HQO Practice Reports. After grouping homes sharing providers together, we anticipate having approximately 160 clusters, with an average of 350 beds per cluster. In a 2 × 2 factorial design assuming no interaction and similar effects for each intervention, a test of each intervention at 6 months in an ANCOVA design will achieve 90% power to detect an absolute mean difference of 0.3 in the primary outcome (i.e. a reduction across arms in the mean number of CNS-active medications from 3 to 2.7). Based on previous data, we have assumed a standard deviation of 4, an intracluster correlation coefficient of 0.05, a cluster autocorrelation of 0.8, and an individual autocorrelation of 0.9 [31]. In the presence of an interaction effect, switching to a 4-arm comparison would require a slightly larger difference of 0.4 in the mean number of medications.

For our secondary outcome (any monthly prescription of antipsychotics), our sample size will achieve 90% power to detect an absolute difference of 1.2% (or a relative difference of 6%) from a reference arm proportion of 20% using six monthly pre- and post-intervention measurements, with an intracluster correlation coefficient of 0.05, a cluster autocorrelation of 0.8, and an individual autocorrelation of 0.9. In the presence of an interaction effect, switching to a 4-arm comparison would require a larger relative difference of 8.5%.

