#### Embedded theory-based process evaluation

The process evaluation involves a mixed-methods approach informed by the UK Medical Research Council’s Guidelines [34] to examine whether the intervention targets the intended constructs outlined in the program theory (Fig. 1) and understand the contextual factors that shape how the intervention works in practice.

To assess fidelity of receipt, we will examine the extent of exposure (i.e. timing and frequency of Practice Report downloads). We propose that exposure (fidelity of receipt) will be a key effect modifier of the intervention.

The intervention’s mechanism of action will be assessed via surveys of participating physicians across all four arms to measure theoretical constructs targeted by the intervention. Targeted constructs include intention, self-efficacy, outcome expectations, descriptive norms, and goal prioritization. To minimize response burden, a single validated question was included to measure each construct for the prescription of targeted medication classes (benzodiazepines, antipsychotics, and CNS-active medications), in addition to medications that the intervention does not directly target (e.g. statins). These will therefore provide the capacity to conduct a multiple-behaviour process evaluation [35] that will examine the presumed mechanisms underlying any changes observed in prescribing and whether these vary by experimental condition. Prospect theory suggests that when physicians make a decision, they consider risky (i.e. the decision to start/stop benzodiazepines), loss-framed messages may have a larger impact on their behaviour than gain-framed messages [19, 36]. At the same time, the importance of coherence between framing and how the recipient is oriented towards promoting gains or preventing harm is emphasized in Regulatory Fit Theory [37]. We assume that most physicians are focused on preventing harm when thinking about high-risk medications. We will include a questionnaire designed to assess whether individuals are promotion- or prevention-focused which has been validated in patient population [38]; we have adapted this tool to focus on healthcare professional behaviour. Responses will we be used to assess whether respondents’ regulatory focus moderates the effect of the feedback framing intervention.

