We will use multiple regression to explore the relationships between hypothesized predictor constructs (Fig. 1) and the dependent variable (intention to appropriately adjust prescribing) controlling for group allocation. We will then compare the post-intervention scores for the constructs across the intervention groups using independent samples *t* tests, conducting separate comparisons for each of the two main effects (message framing and professional comparator). We anticipate that approximately 250 providers will be allocated in the trial and that approximately 40% will download the Practice Reports. With an anticipated survey response rate of 40%, we expect to have 40 questionnaires available for analysis, evenly distributed between arms. With 20 survey responses in each group (presence or absence of each main intervention effect), we will have 80% power to detect a difference of 0.9 standard deviation units in any of the constructs between the two intervention arms using a two-sided *t* test at the 5% level of significance. We will use hierarchical mediation and moderation models to determine whether interventions work through hypothesized pathways to aid interpretations for generalization in various contexts. We will also conduct additional exploratory analyses to assess the impact of measurable provider, patient, and contextual characteristics on the outcomes.

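### Relating download frequency to effect size conditions on behaviour that the assigned report can change; exposure should be fixed before arm-specific content is seen

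*Protocol article*

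**What the plan says.** Three places in the protocol article deal with exposure.

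- **Analysis:** "A planned sensitivity analysis will examine effects by extent of exposure to the intervention". The same sentence glosses this as "fidelity of receipt, which assesses whether physicians downloaded their report". It names no release or time window.
- **Data collection:** the agency that issues the reports will "track the number of times they downloaded the report at each quarterly release". The coded counts will be used to "conduct a sensitivity analysis to examine how intensity of exposure relates to effect size".
- **Embedded theory-based process evaluation:** fidelity of receipt is assessed through "extent of exposure (i.e. timing and frequency of Practice Report downloads", and exposure is put forward as an important modifier of the intervention effect.

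The Analysis section does caution about unmeasured confounding and uncertain power. That caution is attached to the subgroups defined by relative performance and message wording, not to exposure. All primary analyses are by intention-to-treat. The survey sample-size paragraph under Recruitment and data collection expects that "approximately 40% will download the Practice Reports".

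**The concern.** An effect modifier in the usual sense is fixed before randomisation. Download frequency is not. Once a physician opens a report, the assigned comparator and framing are known to that physician, and whether he or she returns for the next release may be a response to them. The protocol's own reasoning makes this plausible. The Background of the abstract says a higher comparator shows a discrepancy to more recipients. The Analysis section expects different reactions to better and worse relative performance. The section on framing says the risk wording and colours were refined so that the emotional response would prompt action.

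If one arm draws more physicians into the frequent-download category, the extra members need not resemble those who would have returned anyway. A comparison of arms within that category, or of effects across categories, then mixes selection with effect. The risk is greater because uptake is expected to be low: if the intention-to-treat result is null, readers will turn to the exposure analysis for an explanation.

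**Working it through.** **1. Reproducing the plan's figures.** Inputs from the Power section: 160 clusters (80 per factor level), m = 350, SD 4, ICC 0.05, cluster autocorrelation 0.8, individual autocorrelation 0.9. Two-sided 5% is assumed, because that section gives no alpha.

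- r = (m × ICC × CAC + (1 − ICC) × IAC) / (1 + (m − 1) × ICC) = (14 + 0.855) / 18.45 = 0.805
- Design effect = 18.45 × (1 − 0.805²) = 6.49, using unrounded r
- SE = 4 × √(2 × 6.49 / (80 × 350)) = 0.0861
- Detectable difference at 90% power = 3.24 × 0.0861 = 0.28. With 40 clusters per arm it is 0.39.

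These agree with the stated 0.3 and 0.4 to one decimal. The survey figure also reproduces: 250 × 0.4 × 0.4 = 40 questionnaires, and 20 per group gives 79% power for 0.9 SD by the exact t calculation.

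**2. Spurious difference from an arm-dependent category (assumed inputs, no true effect).** Suppose a category holds a share pA of one arm and pB of the other, and the extra members differ by g medications from the rest. The bias is (pB − pA) / pB × g. With pA = 0.40 and pB = 0.50:

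- g = 0.25: 0.10 / 0.50 × 0.25 = 0.05
- g = 1.0: 0.10 / 0.50 × 1.0 = 0.20

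**3. Which exposure definitions are vulnerable (null simulation, assumed inputs).** There are 260 physicians, two arms, two releases and 3,000 repetitions, without clustering. Motivation u is standard normal. The change in medications is −0.3u plus noise of SD 0.6, with no treatment effect. The log-odds of download are −0.5 + u. In one arm, the log-odds of downloading again after opening the first report are raised by 1 or 2.

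| Group compared between arms | Shift 1 | Shift 2 |
|---|---|---|
| First-release downloaders | −0.002 | 0.000 |
| Ever-downloaders | −0.002 | 0.001 |
| Repeat downloaders | 0.040 | 0.074 |

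Monte Carlo standard errors are 0.002 to 0.003. The arm that encourages return visits looks worse, because it brings less motivated physicians into the repeat group. Only the frequency-based group is biased.

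**4. Precision of the restricted comparison.** Trial status gives 267 physicians in 160 clusters. At 40% uptake, 0.4 × 267 = 107 physicians download, so at most 107 clusters can hold one. If downloading went by whole clusters, 0.4 × 160 = 64 would.

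- 64 clusters: SE = 0.0861 × √(160/64) = 0.136; power for 0.3 = Φ(0.3/0.136 − 1.96) = 60%
- 107 clusters: SE = 0.0861 × √(160/107) = 0.105; power = 81%

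The second line keeps 350 residents per cluster. Spreading 40% of the 56,000 beds (22,400) over 107 clusters gives 209 each, an SE of 0.106 and still about 81%. Neither count is a strict bound on what will happen: downloaders could be concentrated in fewer than 64 clusters, and first-release uptake could be below 40%.

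**The case against.** The best defence is that the Analysis section's gloss concerns whether a report was downloaded, not how often. A physician who has never opened a report has not seen its comparator or framing, so ever versus never downloaded escapes the mechanism described here, and the simulation agrees. Comparing randomised arms within that stratum is one natural reading of the planned sensitivity analysis. This stands, and it disposes of a stronger reading, that first-release download is the only valid definition. It does not rescue the Data collection and process evaluation sections, which commit to intensity, timing and frequency.

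A reader might also infer that exposure will be accumulated over the whole trial. No window is stated, and fixing one can fairly be left to the analysis plan.

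A third tempting inference is that the 90% power claim fails because of low uptake. If non-downloaders could not respond at all, an overall 0.3 would need 0.3 / 0.4 = 0.75 among residents of downloaders (1.0 at 30% uptake, 0.5 at 60%). A true 0.3 confined to them would dilute to 0.12, with Φ(0.12/0.0861 − 1.96) = 29% power. But the Power section's 0.3 is a difference between arms as allocated, which is what intention-to-treat estimates. Nothing says it is the effect among downloaders, and the Allocation section's account of collaborative working makes some spillover plausible. The remark that "it is necessary to power for small changes" does not alter this. The 40% is used only to size the survey.

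Finally, this is a sensitivity analysis, so no primary estimate or error rate is at risk. That is correct and limits the weight of the point.

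**Conclusion.** The concern holds for analyses by download intensity, timing or frequency. These condition on behaviour that follows sight of the assigned report, and the protocol attaches no caution to them. The possible distortion is modest to material: 0.04 to 0.07 medications in the simulation and 0.05 to 0.20 in the mixture calculation, against a target of 0.3. All of these values rest on assumed inputs and show only what could happen.

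The concern does not extend to ever versus never downloaded, to the primary intention-to-treat result, or to the stated power. Either acceptable definition rests on two conditions that the article does not state: release notices are the same across arms, and physicians do not learn the report's content from colleagues before their own first download. With 267 / 160 = 1.7 physicians per cluster on average, the second condition deserves a sentence. First-release download leaves less time for such sharing and is therefore the simpler choice.

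**What to change.** Keep intention-to-treat as primary and leave the power statement as it is. For the exposure analysis:

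1. Define it as the comparison of randomised arms among residents of physicians whose exposure status is fixed before arm-specific content is seen. First-release download is simplest; ever versus never downloaded is also acceptable.
2. State the two assumptions: identical release notices across arms, and no sharing of report content before first download.
3. Analyse later download counts as an outcome by arm.
4. Label any result relating intensity or frequency to effect size as observational.

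The cost is wording only, since downloads are already recorded by release. The price in inference is that the result applies to downloaders alone and is less precise than the full comparison: roughly 60% to 81% power for 0.3 under the assumption of 64 to 107 clusters with a downloader, and lower if first-release uptake falls short of 40%.

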### Power

In head-to-head trials where small changes to existing initiatives are tested and where each sequential change in the process of optimization is expected to offer cumulative benefit, it is necessary to power for small changes. In this pragmatic trial, the sample size is dependent on the number of providers who sign up for the reports. At the time of study launch, there will be physicians working in over 200 nursing homes who have signed up to receive the HQO Practice Reports. After grouping homes sharing providers together, we anticipate having approximately 160 clusters, with an average of 350 beds per cluster. In a 2 × 2 factorial design assuming no interaction and similar effects for each intervention, a test of each intervention at 6 months in an ANCOVA design will achieve 90% power to detect an absolute mean difference of 0.3 in the primary outcome (i.e. a reduction across arms in the mean number of CNS-active medications from 3 to 2.7). Based on previous data, we have assumed a standard deviation of 4, an intracluster correlation coefficient of 0.05, a cluster autocorrelation of 0.8, and an individual autocorrelation of 0.9 [31]. In the presence of an interaction effect, switching to a 4-arm comparison would require a slightly larger difference of 0.4 in the mean number of medications.

For our secondary outcome (any monthly prescription of antipsychotics), our sample size will achieve 90% power to detect an absolute difference of 1.2% (or a relative difference of 6%) from a reference arm proportion of 20% using six monthly pre- and post-intervention measurements, with an intracluster correlation coefficient of 0.05, a cluster autocorrelation of 0.8, and an individual autocorrelation of 0.9. In the presence of an interaction effect, switching to a 4-arm comparison would require a larger relative difference of 8.5%.

### Economic evaluation

We will conduct a cost-effectiveness analysis from the perspective of the publicly funded health care system. Total costs include costs associated with designing and delivering interventions and health care costs incurred by nursing home residents. We will use a micro-costing technique [32] to identify, measure, and value resources required for the interventions. HQO staff will provide the number and type of resources used for designing and delivering interventions. We will multiply the quantity of each type of resource required by its unit costs to obtain component-specific costs and overall costs for the interventions. Health care costs incurred by nursing home residents will be derived using the costing methodology developed at ICES [33].

We will estimate the incremental cost per unit change in monthly number of CNS-active medications as well as the incremental net benefit of the interventions using a general linear mixed effects regression model. A series of sensitivity analysis will be undertaken to examine the effect of conducting a complete case only analysis and of varying input parameters. Uncertainty in the analysis will be addressed by estimating 95% CIs using a non-parametric bootstrapping method. Results from the bootstrapping exercise will also be used to depict cost-effectiveness acceptability curves, which represent the probabilities that interventions being cost-effective over a range of potential threshold values that the health system may be willing to pay for an additional unit of effect.

#### Embedded theory-based process evaluation

The process evaluation involves a mixed-methods approach informed by the UK Medical Research Council’s Guidelines [34] to examine whether the intervention targets the intended constructs outlined in the program theory (Fig. 1) and understand the contextual factors that shape how the intervention works in practice.

To assess fidelity of receipt, we will examine the extent of exposure (i.e. timing and frequency of Practice Report downloads). We propose that exposure (fidelity of receipt) will be a key effect modifier of the intervention.

The intervention’s mechanism of action will be assessed via surveys of participating physicians across all four arms to measure theoretical constructs targeted by the intervention. Targeted constructs include intention, self-efficacy, outcome expectations, descriptive norms, and goal prioritization. To minimize response burden, a single validated question was included to measure each construct for the prescription of targeted medication classes (benzodiazepines, antipsychotics, and CNS-active medications), in addition to medications that the intervention does not directly target (e.g. statins). These will therefore provide the capacity to conduct a multiple-behaviour process evaluation [35] that will examine the presumed mechanisms underlying any changes observed in prescribing and whether these vary by experimental condition. Prospect theory suggests that when physicians make a decision, they consider risky (i.e. the decision to start/stop benzodiazepines), loss-framed messages may have a larger impact on their behaviour than gain-framed messages [19, 36]. At the same time, the importance of coherence between framing and how the recipient is oriented towards promoting gains or preventing harm is emphasized in Regulatory Fit Theory [37]. We assume that most physicians are focused on preventing harm when thinking about high-risk medications. We will include a questionnaire designed to assess whether individuals are promotion- or prevention-focused which has been validated in patient population [38]; we have adapted this tool to focus on healthcare professional behaviour. Responses will we be used to assess whether respondents’ regulatory focus moderates the effect of the feedback framing intervention.

To gain a more nuanced understanding of how and why the intervention worked as observed, we will conduct qualitative interviews with interested participants. We will examine whether participants view changes in prescribing as a risky behaviour, as assumed, or if they endorse generally positive experiences with prescribing these medications, and perceive their ongoing use as generally safe. We will also probe the underlying mechanisms through which the interventions may influence prescribing behaviour (Fig. 1). The constructs measured in the theory-based questionnaire will be represented within the interview topic guide. Interviews will focus on gaining additional insight into quantitative responses to the constructs assessed in the questionnaire while providing an opportunity for respondents to clarify any additional factors relevant to their experience of using the feedback report allocated to them.

